## Methods

### Design

To study the effects of R&W an RCT design is implemented in the 7th Grade of preparatory vocational education level. Schools from different parts of The Netherlands are randomly assigned to one of three intervention groups or to the control group (Fig. 1). In the ‘Light’ condition a core team of teachers is trained with the three-day training course to become certified R&W trainers and implement the R&W program. In the ‘Standard’ condition a core team is trained to become R&W trainers and the rest of the school-team that teaches 7th Grade students follows a three-day training to learn how they can support the R&W trainers of their school and how they can apply R&W in their regular classes. The ‘Plus’ condition is equal to the ‘Standard’ condition with the addition of a parent component. The parents watch a documentary of R&W, get an invitation to join a lesson in the school, receive weekly e-mails with information about the lesson of that week and are stimulated to act on this information, for instance by communicating about R&W or using R&W language. This will not only create a supporting environment within the school, but also in students’ homes. In the control condition students receive CAU; i.e., current school policy to enhance socio-emotional adjustment and social safety of students.

**Fig. 1 Fig1:**
[figure not shown]
Flow chart

Students receive R&W for two years. The intervention is implemented during physical education classes by (mostly) physical education teachers who followed the three-day training. After successfully terminating this training, these teachers are certified R&W trainers. Socio-emotional adjustment (i.e., psychosocial wellbeing, sexual autonomy, and resilience), social safety (i.e., perceived social security in the classroom, aggression, and bullying), and mediators (i.e., self-control, self-reflection, self-esteem, and emotion regulation) will be assessed at multiple measurement points: Prior, during and after R&W in the first and second year and at follow-up. These concepts are assessed with online questionnaires completed by students, parents, and teachers. The interim measurements (during R&W) are shortened questionnaires and are completed by students after a series of three R&W lessons. Deviant and prosocial communication is assessed in the first year prior and after R&W using video-observations in a subsample. Moderators (i.e., student, teacher, and parent characteristics) are assessed at one time point.

The study is registered with the Dutch Trial Registration (6554) and has been approved by the Ethical Committee of the Faculty of Social and Behavioral Sciences of Utrecht University (FETC17–015).

### Study sample

In total, we aim to include 720 students in this study across all waves, 180 per condition. Participants are students in the 7th Grade, in the second year of the intervention in the 8th Grade, of preparatory vocational education level. Schools are excluded if they currently implement R&W in the whole school or have implemented the intervention in the past two years in the whole school. Additionally, schools for students with special needs are excluded from the study.

### Recruitment

Schools were recruited through the network of the developers of R&W, the Gadaku Institute. An e-mail to certified R&W trainers was sent with information about this study and a message on the private R&W online forum was posted. Trainers asked within their network whether schools that did not implement R&W were interested in participating in this study. When schools were interested they contacted the Gadaku Institute which referred the school to the researchers. The researchers established whether the school was eligible for participation. If the school was eligible, the researcher provided additional information to the schools based on which the school made a decision concerning participation.

Schools were randomly assigned (1:1:1:1 ratio) by stratified block randomization, with blocks of four (i.e., the number of conditions in this study). Schools were stratified by school size (small to moderate sized schools: < 100 students in 7th Grade, large sized schools: > 100 students in 7th Grade) to establish a more equal distribution of students over the four conditions. The randomization numbers were generated by a random number generating computer program.

Students, parents, teachers, and R&W trainers received an information letter to inform them about R&W and the study. Parents also attended a parent-teacher evening where they received additional information about R&W. Students gave active informed consent and parents passive informed consent for participation of the student. Parents gave active informed consent for their own participation in the study. Active informed consent was also acquired for participation of teachers and R&W trainers.

### Conditions

#### Rock and water

The R&W program is based on the theory of ‘the Rock and Water house’ (Fig. 2). According to this theory there are five levels of the house (themes) that are discussed during the intervention: Safety, assertiveness, social skills, intuition, and spirituality. During the theme safety, feeling safe at home, at school and in society is discussed. Safety is important for students’ development and to find their own way. With the theme assertiveness students learn to deal with difficult situations without losing self-control. The third level social skills emphasizes the importance of communication in our contemporary, multicultural society. Intuition is discussed to make students aware of their preferences and choices, made by intuition, that are determinants for their lives based on their qualities, talents and possibilities. The roof of the house (fifth level) is spirituality. In this theme students learn to follow their own path and gain insight in themselves.

**Fig. 2 Fig2:**
[figure not shown]
The Rock and Water house

The foundation of the R&W house is built on three pillars: Self-control, self-reflection, and self-esteem. The R&W theory states that acquiring these three skills forms the basis for further development concerning the five themes. By learning to control and direct their energy (self-control), students are able to reflect on their behavior and the consequences (self-reflection). Knowing that they can control, reflect upon and potentially change their actions, students’ self-esteem increases; they know what they are capable of and what they want.

The themes are handled and discussed using a psychophysical approach within a safe, supportive and respectful environment. R&W emphasizes the safe and supportive environment where students are allowed to make mistakes. Such an environment is expected to encourage students’ exploration and learning, addressing personal needs and problems, and establishing positive relations. Respect within the group and between students is created based on the principles and ethics of martial arts on which the physical exercises are based. Students learn basic self-defense skills in which it is supposed that they train their self-control, learn what to do in violent situations and work together respectfully. Additionally, they practice their non-verbal communication by making eye contact and reading the body language of their partner during the exercises.

In the exercises, special attention is paid to students’ body awareness and level of arousal. R&W aims to make students aware that physical signs such as tensions in the muscles, a-rhythmic breathing, and increased heartrate are expressions of emotions, stress and feelings. It is expected that during R&W they learn how to actively relax, find the source of the tensions and connect to their self-control and emotion regulation. This is explained using the terms ‘rock’ and ‘water’. ‘Rock’ indicates a physical tense and firm position with low breathing (i.e., Being aware of one’s own opinion, thoughts and feelings and being able to resist pressure from others). ‘Water’ implies a relaxed but alert position with low breathing (i.e., Knowing one’s own opinion, thoughts and feelings and open to those of others). Students are encouraged to experience that the ‘rock’ and ‘water’ attitudes are on a continuum which they can use to regulate their behavior and interactions.

The R&W program is implemented in the schools for two years. The program starts in 7th Grade with 14 weekly lessons of one and a half hour. In 8th Grade students receive 8 weekly lessons of one and a half hour (see Table 1 for an overview of the topics per lesson). The lessons are given to the class as a whole in large spaces such as a gym hall or drama classroom. The trainers are (mostly) physical education teachers of the schools whom have participated in the three-day training course provided by the Gadaku Institute. These trained and certified teachers are monitored and supervised during the study by coaches of the Gadaku Institute. These coaches have at least once a week contact with the R&W trainers in the schools by e-mail, telephone, or face-to-face depending on the needs of the trainers. They answer questions and give advice regarding the R&W program. Additionally, the coaches observe a lesson of the trainer and provide feedback based on that observation.

**Table 1 Tab1:** Overview of the Topics of the R&W Lessons in Year 1 and in Year 2

Year 1 (7th Grade)		Year 2 (8th Grade)	
Lesson	Topic	Lesson	Topic
1	Standing strong (Relaxation)	1	Refresh skills year 1
2	Standing strong together (Helping each other in confrontation)	2	Breathing (Relaxation)
3	Physical and mental pressure	3	Body language
4	Bullying (Ignoring)	4	Peer pressure and bullying
5	Bullying (Walking away)	5	Peer pressure (Sexual autonomy)
6	Verbal communication	6	Responsibility and making own choices
7	R&W in school	7	Sexual autonomy (Boundaries)
8	Breathing (Relaxation)	8	Positive thinking and visualization
9	Body language		
10	Personal contact		
11	Experiencing, respecting, and setting boundaries		
12	Experiencing, respecting, and setting boundaries		
13	Intuition		
14	Dealing with intimidating group		

During the lessons, the trainers explain, demonstrate and monitor the exercises indicating what behavior is desired and what is not by giving feedback. The skills and techniques learned in the exercises are repeated over the lessons to enable integration and internalization of these skills in students’ thinking and acting. After an exercise, students reflect in the group upon what they have learned from the exercise and how they could integrate this in their daily lives. Each lesson is ended with a physical condition exercise such as push-ups or jumping rope. In the first lessons, students set individual goals for themselves concerning these physical condition exercises. At the end of the R&W lessons, in 7th Grade and in the 8th Grade, they evaluate if their goals are met or not. After each lesson, students complete homework assignments in their workbook. In this workbook a summary of the lesson and some questions are given to the students. This aims to stimulate the transfer of the taught skills to their daily lives and to practice the skills outside of the lessons.

The physical exercises are performed with different partners which is thought to increase the coherence of the group in which the R&W program is implemented. Students learn how to work and play together as a class. During the exercises they have to control their strength, set boundaries and be respectful towards each other. It is expected that learning how to connect and listen to others while being calm and keeping their strength, they improve their social skills and increase the social support within the class.

#### Control condition

Students will receive CAU: Current school policy to enhance socio-emotional adjustment and social safety of students. In The Netherlands, all schools have such a policy, since it is obligatory. However, the operationalization of the policy can vary widely. Some schools have a program or training other than R&W (e.g., lifestyle lessons), other schools have a policy on management level (e.g., anti-bullying contracts with students).

#### Instruments

An overview of the concepts, instruments, measurement points and informants is presented in Additional file 1: Table S2.

#### Socio-emotional adjustment

To assess psychosocial wellbeing students, parents and (non-trainer) teachers complete the short version (12 items; e.g., “I am stubborn.”) of respectively the Youth Self Report [27, 28], the Child Behavioral Checklist [29, 30] and the Teacher’s Report Form [31, 32] based on the study of Chorpita and colleagues [33]. Additionally, students and parents fill in the subscale Psychological wellbeing (7 items; e.g., “Did you had fun?”) of the KIDSCREEN-27 [34].

Sexual autonomy is reported by the students. For this, items from a national study in The Netherlands concerning sexual health [35] are used. These 5 items represent interaction competence concerning control, assertiveness and self-esteem (e.g., “I have little influence on what happens.”).

To measure resilience, students, parents, and (non-trainer) teachers complete the Connor-Davidson Resilience Scale short version [10, 36]. The 10 items reflect the self-beliefs to cope with difficulties in life (e.g., “Able to adapt to change.”).

#### Social safety

Perceived social security in the classroom is measured using the subscales Comfort (4 items; e.g., “In this class, I can be myself.”), Conflict (4 items; e.g., “In this class, children argue with each other.”), and Cohesion (4 items; e.g., “In this class, everyone likes each other.”) of the Classroom Peer Context Questionnaire [37] completed by students and (non-trainer) teachers. It assesses the perception of school culture, for instance how positive, respectful, friendly and helpful students are towards each other and sense of belonging.

Aggression is measured with the Reactive and Proactive Aggression Questionnaire [38, 39]. It assesses reactive (3 items; e.g., “If they tease or threaten me, I get angry.”) as well as proactive (3 items; e.g., “If I do not like a child, I will bully him with others.”) aggression. Students, parents, and (non-trainer) teachers complete this questionnaire.

To measure bullying, students complete the 2 global items of the Olweus Bully/Victim Questionnaire [40]. It measures the frequency of bullying and victimization. Additionally, students complete brief sociometric nominations assessing social acceptance, popularity and classmates’ roles concerning bullying.

#### Moderators

Students’ gender and ethnicity and trainers’ gender, ethnicity, education, expertise, and degree of received training and supervision are assessed with questionnaires developed for this study.

Students’ personality is reported by the student and parent using the Quick Big Five [41]. It consists of 30 items (i.e., characteristics; e.g., nice, sympathetic, organized) on which the informant can indicate to what extent that characteristic suites the participant.

Parental sense of parenting competence is assessed with the subscale Competence of the Parenting Stress Index [42] completed by the parent. It measures the degree to which parents feel they are capable enough and have enough skills to cope with their child. The subscale contains 8 items (e.g., “Raising my child is harder than I expected.”).

Positive parenting will be measured using the subscales Warmth and Monitoring from the Co-parenting Behavior Questionnaire [43] completed by the parent. The subscale Warmth (7 items; e.g., “I spend time doing fun things with my child.”). measures the extent to which parents show parenting behavior to make their children feel comfortable, accepted and approved. The subscale Monitoring (5 items; e.g., “I know my child’s after school activities.”) measures parental awareness of different aspects of the children’s life.

Teacher’s sense of competence will be assessed with the subscale Self-efficacy for management of the Teachers’ sense of self-efficacy [44] completed by the R&W trainer. This subscale measures teachers’ confidence in their skills to effectively manage their classroom. It contains 6 items (e.g., “How much can you do to control disruptive behavior in the classroom?”).

#### Mediators

Self-control is assessed with the Self-Control Scale short version [45] completed by the student. It contains 11 items (e.g., “I wish I had more self-discipline.”). This questionnaire measures students’ ability to change their inner responses, interrupt undesired behavioral impulses and abstain from acting on these tendencies. Additionally, halfway the questionnaire students complete a shortened version (19 items) of a delayed discounting computer task to measure self-control including a ‘catch’ question [46–48]. Students can choose a smaller, immediate reward or a larger, delayed reward (e.g., “Would you prefer to receive €54 today or in 117 days €55?”). To ascertain that the students have read the questions, a catch question is added, similar in form, amount and delay: “Would you prefer to receive €59 today or in 139 days €21?”

Self-reflection will be reported by the students using the Engage in reflection subscale of the Self-Reflection and Insight Scale [49]. It contains 6 items (e.g., “I don’t often think about my thoughts.”).

Self-esteem will be measured with the subscale Global self-perception of the Self-perception Profile [50] reported by the students. This subscale contains 5 items (e.g., “I’m often disappointed in myself.”).

Emotion regulation is measured using the subscales Impulse control (6 items; e.g., “When I’m upset, I feel out of control.”) and Strategies (8 items; e.g., “When I’m upset, I believe that I will remain that way for a long time.”) from the Difficulties in Emotion Regulation Scale [51] completed by students. These subscales measure students’ ability to control their emotional impulses and the regulation strategies they apply.

Deviant and prosocial communication is assessed using video-observations of same-sex dyads of classmates in a subsample of students in the ‘Standard’ and control condition. This observation task is based on the Peer Interaction Task [52]. The dyads plan an activity together, as warm-up, and subsequently discuss 3 situations concerning daily school situations. Each of these 4 segments lasts 5 min. The 20 min interactions are videotaped and coded. Deviant and prosocial communication is coded based on the Conversation Topic Code [53, 54] and communication ratings [55–57].

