## Discussion

This study protocol presents the design of a study evaluating the effectiveness of R&W in increasing socio-emotional adjustment and social safety in prevocational students. Previous small-scaled research has shown promising results. With this study we try to overcome the limitations of previous studies by incorporating more measurement waves (i.e., prior, during, and after R&W in the first and second year, and at follow-up), and by using a multi-informant (i.e., students, teachers, parents) and multi-method (i.e., questionnaires, computer task, video-observations) approach. We will be in the unique position to not only examine the effectiveness of R&W in different levels of school and parental involvement, but also to study what works for whom, and the working mechanisms of the intervention.

A possible threat to the study that we foresee is reaching and engaging the different informants (i.e., students, parents, teachers). In general, we try to reduce this possible threat by organizing focus groups with participating schools. During these meetings we discuss the feasibility of our plans and ask for suggestions (e.g., "How can we best reach parents?").

In particular, it might be that we ask students too many questions. They could lose their interest and concentration and eventually give answers without reading the questions to finish the questionnaire sooner. We try to diminish this loss of interest and concentration by digitalizing the questionnaire and by adding a computer task halfway the questionnaire. The digital questionnaire enables students to complete the questionnaire on mobile devices which is probably more interesting to the students than filling in the questionnaires on paper. The computer task makes the students feel like they are doing something different than filling in questionnaires, after which they have renewed energy to complete the second half of the questionnaire. Moreover, students can complete the questionnaire during school hours so that it does not cost them additional time.

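### The one catch item described for the delay-discounting task cannot detect a student who answers 'today' throughout without reading

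*Protocol article*

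**What the plan says.** The Mediators section of the protocol article measures self-control with the 11-item Self-Control Scale and, in addition, with "a shortened version (19 items) of a delayed discounting computer task to measure self-control including a ‘catch’ question". On the regular items, "Students can choose a smaller, immediate reward or a larger, delayed reward"; the printed example is "Would you prefer to receive €54 today or in 117 days €55".

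The purpose of the check is stated directly: "To ascertain that the students have read the questions, a catch question is added, similar in form, amount and delay". The item itself, with its lead-in, reads: "a catch question is added, similar in form, amount and delay: “Would you prefer to receive €59 today or in 139 days €21". No other check on careless answering in this task is described.

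The Discussion names the threat that the check is meant to meet. Of students faced with a long questionnaire it says: "They could lose their interest and concentration and eventually give answers without reading the questions to finish the questionnaire sooner".

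Under Statistical analyses, self-control is one of the mediators tested first by ANCOVA and then by latent growth curve mediation. That section does not mention the catch item.

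**The concern.** A check on reading should separate students who read from those who do not, whatever careless pattern the latter follow. This item's correct answer lies on one side of the very choice that the task measures. Choosing 'today' is the impulsive response on every regular item and the correct response on the catch item. Careless answering that happens to look like low self-control is therefore the pattern the item lets through.

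At stake is how far the task-based self-control score can be trusted. An all-'today' record could come from a very impatient student who read everything or from a student who read nothing, and passing the catch item does not tell them apart. The task is also the only non-questionnaire measure of self-control, so it carries part of the multi-method strength that the Discussion claims.

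**Working it through.** The article gives no figure for the performance of the catch item, so there is none to reproduce. The check is one of dominance and simple probability.

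**Inputs (Mediators section).** Regular example: €54 today or €55 in 117 days. Catch item: €59 today or €21 in 139 days.

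**Step 1: is there a sensible reason to choose 'later'?** Under hyperbolic discounting the indifference rate is k = (later/now − 1)/delay.
- Regular example: (55/54 − 1)/117 = 0.00016 per day. This is positive, so either answer can be a real preference.
- Catch item: (21/59 − 1)/139 = −0.0046 per day. Choosing 'later' would need a negative discount rate. 'Today' is larger and sooner, and is the only sensible answer.

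**Step 2: who passes?** For a student who does not read and chooses 'today' with probability p, P(pass) = p.

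| Careless pattern | p | P(pass) | P(caught) |
|---|---|---|---|
| Always 'today' | 1 | 1.00 | 0.00 |
| Random | 0.5 | 0.50 | 0.50 |
| Always 'later' | 0 | 0.00 | 1.00 |

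The catch item is informative for an all-'later' record: a patient student who reads will switch to 'today' on it, and one who does not read will not. For an all-'today' record it is uninformative.

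**Step 3: would excluding students who fail bias the mean score?** The article states no exclusion rule, so this step is purely illustrative. Assume 18 scored items, a score equal to the number of delayed choices, an attentive mean m and an inattentive fraction f split evenly between always-'today' (score 0) and always-'later' (score 18).
- Unscreened mean = (1 − f)m + (f/2)·18.
- Screened mean = (1 − f)m/(1 − f/2).

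| m | f | Unscreened (error) | Screened (error) |
|---|---|---|---|
| 9 | 5% | 9.00 (0) | 8.77 (−0.23) |
| 9 | 10% | 9.00 (0) | 8.53 (−0.47) |
| 9 | 20% | 9.00 (0) | 8.00 (−1.00) |
| 5 | 20% | 5.80 (+0.80) | 4.44 (−0.56) |

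At m = 9, exactly mid-scale, the two careless groups cancel before screening, so removing one of them creates an error. At m = 5 and f = 20%, the same screening reduces the absolute error from 0.80 to 0.56. At f = 20% the screened error is the smaller one whenever 1.8 − 0.2m > m/9, that is for m below about 5.8.

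Two other mixes, both with m = 9:
- If all careless students choose 'today', the mean is 9(1 − f) = 8.55, 8.10 and 7.20 for f = 5%, 10% and 20%. It is the same with or without screening, because nobody is caught.
- If all careless students answer at random, their mean is also 9 and screening leaves the mean unchanged.

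No general statement about the direction or size of a screening bias follows.

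**Step 4: what would a second item add?** If a second item has the delayed option as its dominant answer, P(pass both) = p(1 − p). This is 0 for always-'today', 0 for always-'later' and 0.25 for random answering, against 1, 0 and 0.50 with the single item.

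**The case against.** The strongest defence is that the harm depends on matters the article does not state. It gives no scoring rule, no rule for students who fail and no on-screen order, and a condensed article may properly leave these to a fuller document. If the position of the options varies on screen, a student who clicks one position is not an all-'today' responder and may be caught. This stands, and it limits what can be said about consequences. It does not rescue the item for a student who chooses by the word 'today', because the item and its purpose are printed and its dominant answer does not depend on layout.

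The defence is also right on importance. The task is additional to the Self-Control Scale, serves one of several mediators and is not an outcome under the first aim. A shift that is equal across conditions would largely cancel in comparisons between conditions, and nothing in the article suggests that careless 'today' answering differs by condition. The Discussion also describes mitigation: a digital format, a task placed halfway to renew attention, and completion in school hours.

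A reader might infer two stronger points. One is that the item catches only always-'later' students; in fact random responders are also caught about half the time. The other is that screening on the item adds bias rather than removing it. That would need an exclusion rule the article does not contain, and even under an assumed rule the result reverses with the assumed attentive mean and mix of careless patterns.

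**Conclusion.** The point holds in a limited form and is minor. The single catch item described does not by itself achieve its stated purpose, because it passes every student who chooses 'today' throughout without reading. This rests only on the printed item and needs no assumption about scoring, layout or exclusion.

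That such a student would be scored as having the lowest self-control is an inference from how the task is built, since no scoring rule is given. The direction and size of any effect on the self-control score or the mediation result cannot be determined from the article. The figures in the third step of the working are illustrations under assumed values, not estimates for this trial.

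**What to change.** Do not rely on the single catch item alone. At every wave in which the task is given, flag students whose choices are all 'today' or all 'later'. Report the task-based self-control and mediation results with and without flagged and catch-failing students, as a sensitivity analysis. This needs no new data and costs one derived variable and one repeated analysis.

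In any remaining waves, optionally add a second catch item whose clearly dominant answer is the delayed option, for example €0 today or a positive amount later. It must keep a 'today' option: an item offering two amounts at the same delay would catch only students who click one position, and that depends on the screen layout. The cost is one more item per wave, and a zero amount looks somewhat less like the regular items.

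The main downside is that some attentive, truly very impatient students will be flagged. The flag should therefore drive the sensitivity analysis and not lead to automatic exclusion.
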